##### Retrospective assessments

In this experimental manipulation, participants will be asked to complete retrospective assessments only. A retrospective assessment will be defined as a single administration of the EPDS.

Participants will be required to complete assessments for a total of 6 months, and each assessment period will consist of 1 day. The 6-month participation period will be calculated from the day on which the app is activated (ie, when participants enter their activation code and activate their account), and it will be divided into six intervals. Again, all participants will receive the first notification 2 days after activating BrightSelf (ie, first assessment). Subsequent assessments will take place on a random day within the 21–35 days following the end of the previous assessment period (in order to avoid two consecutive EPDS assessments).

On each assessment day, participants will receive a notification to complete the EPDS at a random time between 17:00 and 21:00.

At the end of the 6-month period, participants will be sent a link via SMS or by e-mail to complete the non-validated, poststudy acceptance survey (see figure 3 for an illustration of both sampling protocols).

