##### Duty of care

Regardless of participants’ allocation, the central research team will be alerted if any of a series of prespecified conditions are met (table 2). These alerts will be colour-coded according to their severity level. In order to determine the severity level, we have chosen commonly used EPDS scoring thresholds (ie, 10–12 points for possible depression, and 13 points or more for probable depression). We acknowledge the limitations of this approach as the diagnostic accuracy of the EPDS can vary depending on the setting and the population in which it is administered.

**Table 2 T2:** Criteria for an alert to be sent to the research team

**Type of alert**	**Criteria**
Yellow (Mild)	Completing more than one EPDS assessment on the same day, with an overall EPDS score of 9 points or less and a score of 0 on question 10 of the EPDS
Orange (Moderate)	Overall EPDS score between 10 and 12 points, with a score of 0 on question 10 of the EPDS
Red (Severe)	Overall EPDS score of 13 points or more, and 1 or more points on question 10 of the EPDS, regardless of the overall EPDS score

EPDS, Edinburgh Postnatal Depression Scale.

Before starting the study, the central research team will agree on a list of designated contacts with the relevant clinical care teams. These contacts will include clinicians who are available during normal working hours, as well as those on duty outside working hours (including weekends and bank holidays). If a red or orange alert is generated, the study coordinator will contact the designated member of the clinical care team by phone and e-mail within 24 hours of receiving the alert. The clinical care team will then follow up these alerts directly with the participants.

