#### Inferential statistics

We will compare the *retrospective and momentary assessment* and the *retrospective assessment* experimental groups for differences in adherence rates, dropout rates and timeliness of data completion. For this we will use a t-test or the non-parametric equivalent.

We will compare acceptance between the two experimental manipulations by assessing differences in participants’ rankings to those questions on a 7-point Likert scale of the poststudy acceptance survey. We will also conduct a thematic analysis of the open-ended questions of this survey.

In relation to the momentary assessments, we will examine the distribution of delays between the time of notification and time of report in order to assess the effect of this delay on the ecological validity of reports.

We will analyse usage patterns through regression modelling of log data. We will analyse participants’ momentary and retrospective assessments through time-based analyses or multilevel modelling.^33 34^ We will attempt to compare if the momentary assessments had any effect on the retrospective assessments by comparing the EPDS responses given on day 1 to those given on day 6.

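### The Day 1 versus Day 6 EPDS comparison cannot separate the effect of momentary assessment from alert-driven clinical contact among high scorers

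*Protocol article*

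**What the plan says.** **Alerts (Duty of care, Table 2).** "Regardless of participants’ allocation, the central research team will be alerted if any of a series of prespecified conditions are met". An orange alert is defined as "Overall EPDS score between 10 and 12 points, with a score of 0 on question 10 of the EPDS"; higher totals and any positive answer to item 10 are dealt with under red. For orange and red alerts, "the study coordinator will contact the designated member of the clinical care team by phone and e-mail within 24 hours of receiving the alert". Then: "The clinical care team will then follow up these alerts directly with the participants". No time limit is given for that last step. A yellow alert does not lead to this contact.

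**EPDS schedule (Retrospective plus momentary assessments; Retrospective assessments).** Each momentary-arm period has one EPDS on Day 1 and one on Day 6, both prompted between 17:00 and 21:00, with momentary questions on Days 2 to 5. In the retrospective arm "each assessment period will consist of 1 day", with a single EPDS. In both arms the 6 months are split up in the same way: "it will be divided into six intervals".

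**Analysis (Inferential statistics).** The plan will attempt to find out whether the "momentary assessments had any effect on the retrospective assessments by comparing the EPDS responses given on day 1 to those given on day 6". The abstract lists this question among the study's aims. The section also names multilevel modelling for the momentary and retrospective data. It does not say how alerted women enter the Day 1 to Day 6 comparison.

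**The concern.** The Day 1 to Day 6 change is meant to show what four days of momentary questions do to the EPDS. Within those days the protocol also sets off a clinical process, and it does so for the women whose Day 1 score was high. If the contact that follows lowers their Day 6 score, the fall is counted as an effect of momentary assessment. The retrospective arm has no Day 1 and Day 6 pair, so no control contrast can subtract it.

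At stake is one stated aim of the study. The adherence, dropout, timeliness and acceptance comparisons are not put in doubt by this point.

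**Working it through.** **Inputs from the protocol**
- Day 1 EPDS notification: 17:00 to 21:00. First Day 2 notification: 09:00 to 12:00. Day 6 EPDS notification: 17:00 to 21:00.
- A form counts as answering its notification if it is completed before the next one (Timeliness of data completion).
- Coordinator to care team: within 24 hours of receiving the alert.
- 96 women per arm (Sample size calculations). This reproduces as 1.96² × 0.5 × 0.5 / 0.10² = 96.04, reading the stated interval of 10 as plus or minus 10 points. It is used here only as a scale for the standard error.

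**Step 1: timing.** Count hours from 00:00 on Day 1 and assume the alert is received when the form is completed.
- Latest completion of the Day 1 form in its window: 12:00 on Day 2 = hour 36.
- Care team contacted by 36 + 24 = hour 60 (12:00 on Day 3).
- Earliest Day 6 EPDS: 5 × 24 + 17 = hour 137.
- Gap: 137 − 60 = 77 hours at least. For a form completed by 21:00 on Day 1 it is 137 − 45 = 92 hours.

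The care-team notification therefore comes before the Day 6 form. The contact with the woman may or may not.

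**Step 2: possible shift.** The protocol gives no alert rate and no effect of contact, so these are assumptions: alert rate per form p = 7%, 12% or 20% (the Introduction's 7% to 12% is depression prevalence and only a rough guide); contact lowers an alerted woman's Day 6 score by 3 points; EPDS standard deviation 4.5; Day 1 to Day 6 correlation r = 0.80 to 0.90; no effect of momentary assessment.
- Women alerted on Day 1 per period: 96 × 0.07 = 6.7 to 96 × 0.20 = 19.2.
- Shift in the mean change = −3p: −0.21, −0.36 and −0.60 points.
- Standard error for one period = 4.5 × √(2(1 − r)) / √96: 0.29 at r = 0.80 and 0.21 at r = 0.90.

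The false effect runs from about one standard error or less to nearly three (0.60 / 0.21 = 2.9).

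**Step 3: why splitting by Day 1 alert does not solve it.** Suppose neither contact nor momentary assessment has any effect. With Day 1 alerts defined by a threshold on a normal score, the expected fall in alerted periods is 4.5 × (1 − r) × φ(z)/p, and the rise in the others is that fall × p/(1 − p).
- p = 0.07, r = 0.80: φ(z)/p = 1.918, so the fall is 4.5 × 0.20 × 1.918 = 1.73 and the rise is 1.73 × 0.07/0.93 = 0.13.
- p = 0.20, r = 0.90: φ(z)/p = 1.400, so the fall is 4.5 × 0.10 × 1.400 = 0.63 and the rise is 0.63 × 0.20/0.80 = 0.16.

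Regression to the mean alone moves the two groups in opposite directions.

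**Step 4: what works under the same assumptions.** Keep every Day 1 score, including the one that triggered the alert, and treat scores after the trigger as missing. Missingness then depends only on an observed score. A likelihood-based model learns the Day 1 to Day 6 relation from the women not alerted and applies it to the full Day 1 distribution. With a 3-point contact effect and no momentary effect, the simulated estimate of the Day 1 to Day 6 change is within 0.01 points of zero at every setting of p and r above.

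**The case against.** **The article is condensed, and the comparison is tentative.** A missing sensitivity analysis would normally be left to the analysis plan, and this is a feasibility study. That lowers the weight of the point but does not remove it. The article names the contrast, and as named it cannot distinguish the two influences.

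**Contact before Day 6 is not certain.** This stands. The 24-hour limit covers coordinator to care team only. The EPDS also asks about the past 7 days, so a Day 6 form still covers some days before any contact. The claim is that contact can fall in the window, not that it does.

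**The doubled EPDS schedule.** A reader might infer that, because the momentary arm is scheduled for 6 × 2 = 12 EPDS against 6 × 1 = 6, the extra alert opportunities bias the trial's comparisons generally. The documents do not support that. The Day 1 to Day 6 contrast lies within one arm, so the imbalance cannot enter it. For dropout and acceptance, the trial compares assessment strategies, and the alerts that a strategy generates belong to it. The imbalance matters only if later EPDS scores are compared between arms and read as an effect of the momentary questions alone. The article names no such comparison.

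**The whole observed change could be alert follow-up.** A reader might go this far too, but nothing in the documents measures the effect of contact. The figures above show only that the shift could matter.

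**Conclusion.** The point holds for the Day 1 versus Day 6 comparison. The protocol places a clinical notification, directed at high scorers, between the two forms whose difference is to be read as the effect of momentary assessment, and no control pair exists to remove it. The possible shift is 0.2 to 0.6 points against a standard error of 0.2 to 0.3 in one period. It rests on an assumed 3-point contact effect, alert rates of 7% to 20%, a standard deviation of 4.5 and contact before Day 6. The exclusion of women with a current or recent mood disorder could put the true alert rate lower. This is worth correcting before analysis because the remedy is cheap, but it affects one secondary question and not the feasibility outcomes.

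**What to change.** In the Inferential statistics section:

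1. Keep the all-data Day 1 to Day 6 estimate. Beside it, fit a likelihood-based multilevel model to each woman's EPDS up to and including the form that triggers her first orange or red alert, with the triggering score kept in the model.
2. State that a Day 1 to Day 6 change will not be attributed to momentary assessment if it appears only in the all-data estimate.
3. Report orange and red alerts by arm, per woman and per EPDS completed.
4. Do not base the conclusion on agreement between periods with and without a Day 1 alert; regression to the mean makes them differ even when nothing is happening.

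**Cost.** A few lines of analysis on the EPDS scores and the colour-coded alerts they generate. The companion analysis uses fewer EPDS, so it is less precise, and an effect absent from it may be missed and not truly nil; the two estimates should be shown with their intervals. It also relies on the model for high scorers, including where item 10 and not the total sets off the alert. It removes alert-driven contact only, and no other cause of change between the two days. The alert and care rules stay as they are.

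Dates of contact between the care team and the woman would sharpen this, but the article does not say that they are returned to the study, so the fix does not depend on them.

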### Randomisation

We will use block randomisation procedures (with blocks of four) to allocate participants to one of the two experimental arms. Random numbers will be generated using Stata V.14.^31^ Each consecutive number will be embedded within the nine-digit activation codes that will be distributed to each participating NHS site. The full activation codes will be generated in the same order in which the random numbers were generated. Each NHS site will receive a list of activation codes on a first-come-first-served basis. Members of the local research teams will not be informed of the random sequence generation and will not be able to identify which number determines participant allocation. They will be required to use activation codes sequentially, as participants are recruited. Activation codes referring to the *retrospective plus momentary assessment* condition will activate a version of BrightSelf in which both the *Check Back* and the *Check In* features are active. Activation codes referring to the *retrospective assessment* condition will activate a version of BrightSelf in which only the *Check Back* feature is active.

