After obtaining consent, participants will be asked to self-complete a baseline assessment using a tablet computer. This assessment will consist of a (1) sociodemographic survey, (2) the Whooley questions and (3) the EPDS (see online supplementary appendix 1). The last two instruments are recommended by the NICE to screen for depression during pregnancy.^23^ Subsequently, the CSO or research midwife will guide participants through the process of downloading (from either the Apple AppStore or Google Play Store) and installing BrightSelf onto their own handsets. To this end, they will be able to use a recruiter booklet provided by the central research team (see online supplementary appendix 2). In order to activate the app, participants will need to enter a nine-digit activation code, which will also be provided by the central research team.

10.1136/bmjopen-2016-014469.supp1Supplementary appendix 1

10.1136/bmjopen-2016-014469.supp2Supplementary appendix 2

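### Fixed blocks of four, with the allocation carried in ordered activation codes held at sites, could let a recruiter who tracks past allocations foresee up to a third of them

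*Protocol article*

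**What the plan says.** The Randomisation section of the protocol article fixes a single block size: "We will use block randomisation procedures (with blocks of four) to allocate participants to one of the two experimental arms". It then describes how the sequence reaches the sites:

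- The allocation travels inside the code: "Each consecutive number will be embedded within the nine-digit activation codes that will be distributed to each participating NHS site".
- The order is kept: "The full activation codes will be generated in the same order in which the random numbers were generated".
- Sites hold codes ahead of use: "Each NHS site will receive a list of activation codes on a first-come-first-served basis".
- Sites work down the list: "They will be required to use activation codes sequentially, as participants are recruited".

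The arms look different once the app is opened. Codes for the retrospective assessment "condition will activate a version of BrightSelf in which only the" Check Back feature works; codes for the other arm switch on Check In as well.

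Under Sample selection and recruitment, "the CSO or research midwife will guide participants through the process of downloading" and installing the app, after consent and the baseline assessment. The participant enters the code.

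The protocol also states a safeguard: "Members of the local research teams will not be informed of the random sequence generation and will not be able to identify which number determines" the allocation.

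**The concern.** The person who approaches and enrols women also holds the ordered codes and is at hand when the app is set up. The next allocation in a block of four depends on the earlier ones. A recruiter who notices which version opened for recent participants therefore has information about the next code without understanding anything in the code itself. The safeguard addresses decoding and leaves this route open. The block size is also printed in the public protocol.

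The arms differ greatly in burden, and the main outcomes are completion of every expected assessment and completion of the 6-month period. Both depend strongly on motivation. If recruiters expecting the heavier arm approach different women, or change the timing of enrolment, even without intending to, the arms could differ in motivation at entry. That difference would be read as an effect of the sampling protocol. Participants cannot be blinded to the number of assessments, so concealment of the next allocation is the main protection against this selection.

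**Working it through.** **Inputs.** From Randomisation: one block size of four, ordered lists, sequential use. From Sample size calculations: 96 per arm (so 1:1), 192 in total, recruitment target 250. From the two arm descriptions: six assessment periods, with two EPDS administrations plus three momentary assessments on each of four days in one arm, and one EPDS in the other. The Randomisation section gives no predictability figure to reproduce.

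**Burden.** 6 × (2 + 4 × 3) = 84 assessments against 6 × 1 = 6.

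**Step 1: share known with certainty, with past allocations and block starts known.** There are six possible 1:1 blocks of four. In AABB and BBAA, places 3 and 4 are forced. In ABAB, ABBA, BAAB and BABA, only place 4 is forced. Forced places: 2 × 2 + 4 × 1 = 8 of 6 × 4 = 24, or 33.3%. That is 64 of 192, or about 83 of 250.

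**Step 2: best guess under the same conditions.** Always guess the arm that is behind.

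- Place 1: 1/2.
- Place 2: 2/3.
- Place 3: 1/3 × 1 + 2/3 × 1/2 = 2/3.
- Place 4: 1.

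Mean: (0.500 + 0.667 + 0.667 + 1.000) / 4 = 0.708, against 0.500 by chance.

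**Step 3: block size known, block starts unknown.** The protocol does not say that lists are issued in whole blocks. List lengths are not given either, so a range is shown. The guesser updates the probability of each possible place in the block after every allocation seen (4,000 simulated lists per row).

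| Codes on the list | Certain in advance | Best guess correct |
|---|---|---|
| 8 | 4% | 65% |
| 12 | 8% | 67% |
| 20 | 15% | 69% |
| 40 | 23% | 70% |

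**Step 4: past allocations not seen.** Prediction from blocks falls to chance, 50%.

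**Step 5: what varied block sizes achieve.** Assume sizes of 4, 6 and 8 at random, a run of 20 allocations all seen by the recruiter, and a guesser who knows the set of sizes. The certain share falls to about 2% with the first block start known and 0.2% with it unknown. Correct guesses fall only to about 67% and 65%. Varied sizes mainly remove certainty; they lower better-than-chance guessing only slightly.

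**The case against.** The strongest reply has five parts.

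1. **Sight of the version is not stated.** Staff guide installation, but the participant enters the code, and nothing says that staff watch or record what opens. This stands: it is an inference, and without it block-based prediction is at chance. Equally, nothing keeps recruiters from seeing it.
2. **The safeguard claims inability, not just silence.** Keeping the sequence generation from local teams may also be meant to cover the block size. This stands in part, but the protocol itself publishes the block size, and guessing the arm that is behind needs no knowledge of the code.
3. **33% and 71% are ceilings.** They need all past allocations and the block starts. This stands, and the table shows the lower values.
4. **There is limited room to steer.** Women have at least 24 hours to decide, and consent and baseline come before activation. Selection would have to act through whom staff approach, when they enrol them, or use of codes out of order. This narrows the route without closing it; the article does not say how sequential use is enforced.
5. **Other protections exist.** The main adherence and dropout proportions use everyone randomised, and the system records completion. These guard against later exclusions and biased recording, not against selection before allocation.

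A reader might go further and infer that staff could read the arm directly from unused codes by matching digits to app versions. The documents do not support that. They give neither the code format nor the rule linking the embedded number to an arm, so decoding can be neither shown nor excluded, and no figure for it is warranted.

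**Conclusion.** The point holds as a weakness in allocation concealment. Fixed, published blocks of four, ordered code lists at sites and visibly different app versions make upcoming allocations partly predictable to a recruiter who tracks past ones. The upper limit is one third known with certainty and 71% guessed correctly. With block starts unknown, the certain share is about 4% to 23% for lists of 8 to 40 codes, and correct guesses are about 65% to 70%.

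This rests on the plausible but unstated assumption that recruiters learn which version opened. The documents do not show that anyone would act on a prediction, and the size of any resulting bias cannot be computed from them. The change is worth making because it is cheap and the outcomes are sensitive to who is enrolled.

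**What to change.** Make activation codes carry no allocation information. Let the existing BrightSelf backend assign the arm only when a code is activated, after consent and baseline. Draw assignments from one central sequence, run across sites in order of activation, with randomly varied block sizes that are not disclosed to sites. A held code then reveals nothing. Where several sites recruit, staff at one site also see only part of the sequence, which weakens prediction from past allocations beyond Step 5.

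Do not generate a separate sequence per site: each site would then begin at a known block start, which is the condition behind the 33% ceiling.

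**Cost.** A regenerated code list and a small backend lookup. Sample size, outcomes and what participants do are unchanged. Possible imbalance grows slightly: with complete blocks of four the arms differ by at most 2 at any time, and with blocks of up to 8 by at most 4. Balance within a site is no longer held by the blocks. Some better-than-chance guessing remains.

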### Outcomes

#### Adherence to sampling protocols

We will calculate the number of participants who complete 100% of the expected assessments (as per the study protocol) as a proportion of the total number of participants who were randomised into the study. We will subdivide this outcome by using the total number of participants who complete the 6-month participation period as the denominator.

